#### Symptoms of anxiety and depression

The Revised Child Anxiety and Depression Scale (RCADS; [39]) will be used to measure symptoms of anxiety disorders and depression. This will be completed at pre, post and follow-up appointments by young people and parent/s/carer/s, and additionally by the young people at every treatment session. The RCADS is a 47-item parent and child report scale which assesses symptoms of Separation Anxiety Disorder, Social Anxiety Disorder, Generalised Anxiety Disorder, Panic Disorder, Obsessive Compulsive Disorder and Major Depressive Disorder. Responders rate how often each item applies on a scale of 0 (‘never’) to 3 (‘always’). The RCADS has been shown to have robust psychometric properties in children and young people from 7 to 18 years of age [40].

#### Functional impairment

The Child Anxiety Impact Scale (CAIS; [41]) will be used to determine the extent to which anxiety interferes in the young person’s life. This will be completed at pre, post and follow-up appointments by young people and parent/s/carer/s. This measure covers three psychosocial domains (academic, social activities and home/family environments) and consists of 27 items rated on a 4-point scale There are versions for children/adolescents and parent/s to complete, both of which have been shown to have good psychometric properties [41, 42]. Internal consistency for the CAIS-c/p was good to excellent across assessment time points (CAIS-C *α* = .85–99; CAIS-P *α* = .93–95).

The Clinical Global Impression Scale-Improvement (CGI-I; [43]) will be used after the 3-month follow-up assessment to assess the young person’s post-treatment changes in global functioning. This asks the clinician to rate how improved the patient is compared to their initial assessment, prior to treatment, on a scale of 1 (very much improved) to 7 (very much worse). Final scores will be dichotomised to represent ‘much or very much improved’ versus ‘other’. A second rater will independently rate the CGI-I for all participants in order to establish inter-rater reliability.

#### Disorder-specific measures (ACTA only)

Young people in the ACTA treatment arm will also complete up to three disorder-specific measures (for their primary anxiety disorder) to measure symptoms, cognitions and safety behaviours, in order to guide the treatment sessions. The cognitions measure for each disorder will be administered at each treatment session. Symptom and safety behaviour measures will be administered pre-treatment, mid-way through treatment, post treatment and at the booster assessment. Measures that have been designed for use with adults will be adapted for use with adolescents on the basis of consultation with young people. A detailed list of the measures used can be found in Appendix 2.

#### Session-by-session measures to guide treatment (both treatments)

The Outcome Rating Scale (ORS; [44]) will be used to assess functioning across different areas of the young person’s life. It has four items: symptom distress, interpersonal wellbeing, social role and overall wellbeing. Each item is rated using a ten-centre visual analogue scale, with instructions to place a mark on each line. A higher score indicates better functioning. It has good reliability and validity with an adolescent population [45].

The Session Rating Scale (SRS; [46, 47]) assesses key dimensions of an effective therapeutic relationship and is given at the end of each therapy session to obtain feedback from young people and parent/s/carer/s so that any issues related to therapeutic alliances can be immediately identified and addressed. It comprises four rating scales (relationship with the therapist, goals and topics, approach or method and an overall rating) and uses the same visual analogue scales as the ORS. It has well-established reliability and validity [47, 48].

The Goal Based Outcomes tool (GBO; [49]) enables the young person to set up to three goals at the beginning of treatment as a way of evaluating their progress. Progress towards individual goals is then periodically rated on a scale from 0 (no progress) to 10 (goal has been reached). Although this measure is now widely used in CAMHS, its psychometric properties have not yet been established.

#### Service satisfaction

At the end of treatment and at the 3-month follow-up assessment, participants will rate their satisfaction with the service that they have received using the Experience of Service Questionnaire (ESQ; [50]), a measure that was developed by the Health Care Commission as a means of measuring service satisfaction in CAMHS. There are versions for young people and their parent/s/carer/s to report on the extent to which they agree with 12 statements looking at what the respondent liked about the service, what they felt needed improving, and three free-text sections for any other comments. It is routinely used within CAMHS and has been demonstrated to have good psychometric properties [51].

#### Health economic measures

Health economic measures as detailed below are collected from parent/s and young people on the pre, post and 3-month follow-up self-report questionnaires. Clinicians will use logs at each treatment and supervision session and any other times as required.

A societal perspective for costs will be adopted and patient-level resource use data will be collected from parent/s/carer/s on a Client Services Receipt Inventory (CSRI) using patient-health diaries to facilitate recall of healthcare resource use and also from clinicians and supervisors on Economic Logs. This data will be provided by clinicians and parent(s)/carer(s) and will include all health and social care cost-generating resources (e.g. staff time for provision of treatment, training and supervision, GP use, referrals and other relevant services identified), non-NHS cost-generating services (e.g. educational services) as well as leisure and lost productivity time estimates for the parent/s/carer/s (e.g. days off school/college/work).

The EuroQol (Quality of Life) (EQ-5D-5 L) [52] is a well-validated preference-based measure of health-related quality of life, designed to estimate quality-adjusted life years (QALYs), that is widely used across disease areas. The EQ-5D questionnaire contains five simple questions each concerned with a different domain of everyday life, i.e. mobility, self-care, usual activities, pain/discomfort and anxiety/depression. For each domain the respondent has to indicate whether they experience no problems, slight problems, moderate problems, severe problems or extreme problems. The respondent’s answers provide a description or profile of the respondent’s quality of life, and a weight or value can then be placed on each profile using an existing UK tariff derived from the general public [52, 53]. The full questionnaire also includes a visual analogue scale (VAS) for participants to rate their overall health on a scale from 0 (‘worst imaginable health’) to 100 (‘best imaginable health’). The quality of life of carers will be assessed using the EQ-5D-5 L self-report. The EQ-5D-Y [54, 55] was adapted directly from the EQ-5D to estimate utility values for young people (from 8 years). It covers the same domains as the EQ-5D, but the wording of the questions in each dimension is modified to make it appropriate to a younger age range. Both the EQ-5D-5 L and the EQ-5D-Y have established feasibility and reliability [52, 53].

The Child Health Utility 9D (CHU-9D; [56, 57]) is a paediatric measure of health-related quality of life, which allows the calculation of QALYs for use in cost utility analysis. It includes nine dimensions (worried, sad, pain, tired, annoyed, schoolwork, sleep, daily routine, activities) each with five levels. The measure was originally developed with children aged 7–11 years, and subsequently validated in an adolescent population (11–17 years) [57, 58]. The CHU-9D is also available in a ‘proxy’ version for parent/ carer completion, and this will also be used.

#### Treatment credibility

Participant expectancies and views regarding treatment credibility will also be assessed prior to treatment through a credibility and expectancy for improvement scale [24]. This consists of three items, rated on a scale from 0 (not at all) to 10 (completely), asking about how logical the treatment seems, confidence in its success at reducing their symptoms, and their likelihood to recommend the therapy to a friend with similar symptoms.

#### Therapy Content Checklist

To establish that the therapies in each arm are distinct from one another, a checklist of the components of each therapy will be given to therapists to complete at the end of every treatment session. The checklist has been designed for this trial and has 27 items that are distinct to either ACTA (12 items, e.g. development of an idiosyncratic version of the cognitive model) or group CBT (15 items, e.g. cognitive restructuring using thought records). Therapists will indicate which components were carried out in the session that they have just completed. The ratings will be used to compare the content of the ACTA and the Chilled Group sessions in order to determine their distinctiveness.

#### Qualitative interviews

Qualitative interviews will be conducted post treatment to explore young people’s and parents’ experiences of treatment and the research process. Interviews with young people will follow a predetermined topic guide.

### Sample size

Guided by previous successful feasibility studies comparing similar interventions [59–62], the sample size of 48 (with 24 participants in each arm) is considered to be sufficient to provide an estimate of variation in outcomes (on both continuous and dichotomous variables) on which to power the definitive trial, if indicated. It is also considered sufficient to indicate if any adverse events or significant deterioration were likely to occur. As this is a feasibility study, many of the outcome measures are descriptive (e.g. recruitment rates, acceptability of treatment, dropout rates). The outcome variables will be used mainly to determine the viability of running a full-scale RCT. Any results from hypothesis testing comparing the outcome of the two treatments will be treated as preliminary and interpreted with caution as no formal power calculations have been carried out [63]. A subsample will be involved in qualitative interviews after the treatment has been delivered. We will use purposive sampling and sample according to the methodological approach; this is likely to involve around six to ten young people and around four to six parents/carers from each treatment arm.

### Data analysis

#### Analysis of clinical outcomes

Analysis of the feasibility study will primarily investigate recruitment and retention rates, presented as a Consolidated Standards of Reporting Trials (CONSORT) diagram providing both overall and individual arm results at all assessment points. Clinical outcomes will be represented using descriptive statistics for each study arm. An exploratory comparison of between-group differences will be undertaken to assess whether the observed effect size is in line with our expected effect based on the literature, using analysis of covariance or a suitable alternative. Ninety-five percent confidence intervals will be constructed for the between-group differences for each of the outcomes, adjusted for baseline, and compared with the literature. Where differences exist, further investigation of both the group means and variances will be undertaken. Data on the proportion of missing data will also be presented. Where available, the overall baseline clinical data will be compared with routinely available service-level data for adolescents with a primary diagnosis of an anxiety disorder in order to assess the representativeness of trial participants.

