### Randomisation

Consenting participants will be randomised to receive individual sessions of cognitive therapy (ACTA) or group-CBT sessions from the Cool Kids ‘Chilled’ Group treatment [23]. Simple randomisation will be adopted by way of numbered, sealed envelopes prepared before recruitment commences. The allocation sequence will be determined using computer-generated random numbers. In order to minimise bias, the researcher allocating the participant will be blind to the contents of the envelope. Participants will be informed of their allocation immediately following their consent to take part in the study.

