### Treatment

Once randomised, participants will be allocated to a clinician for the relevant treatment arm. Clinicians delivering the trial interventions will be psychological wellbeing practitioners or clinical psychologists and will only deliver treatment in one arm of the trial. The clinician will either arrange treatment session dates with the family (in the case of ACTA), or inform the family of the dates when the next CBT group will run (in the case of Chilled). A letter will also be sent to the participant’s general practitioner (GP) to inform them of the young person’s participation in the research study. For the group, all treatment sessions will take place at the AnDY Research Clinic. For ACTA, treatment sessions will take place at the clinic, but later on in treatment, sessions may take place off-site (e.g. at school, in a café or on public transport) in order to facilitate meaningful behavioural experiments.

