#### ‘Chilled’ Group: Cool Kids ‘Chilled’ Child and Adolescent Anxiety Programme

The Adolescent version of the Cool Kids Child and Adolescent Anxiety Programme [23], known as ‘Chilled’, is a well-established anxiety management programme that teaches CBT techniques for managing anxiety. This has been adapted to be delivered in eight group sessions lasting from 90 min to 2 h (rather than ten 90-min sessions as outlined in the treatment manual), supplemented by the two parent sessions as per the treatment manual (a total of 20 h). Topics that are covered include: psychoeducation, thoughts and feelings, realistic thinking, exposure, managing emotions, problem-solving and, at the final session, relapse prevention. Treatment will be delivered by two clinicians in small groups (ideally with between four and six young people), each week over 8 weeks. The two parent sessions are delivered concurrently to the adolescent sessions on weeks 3 and 8 by one of the clinicians. There is also an additional booster session for the adolescents, 12 weeks after the end of treatment.

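### Chilled is delivered in therapy groups and ACTA individually, but the only model named for the between-arm 95% CIs is ANCOVA and group clustering is not mentioned, so the intervals may be somewhat narrow and the group-arm design effect for the definitive trial is not provided for

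*Protocol article*

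**What the plan says.** The two arms differ in format. Under Randomisation: "Consenting participants will be randomised to receive individual sessions of cognitive therapy (ACTA) or group-CBT sessions". The section on the Chilled group says: "Treatment will be delivered by two clinicians in small groups (ideally with between four and six young people), each week over 8 weeks". Under Treatment, each clinician "will only deliver treatment in one arm of the trial"; the number of clinicians is not given.

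Under Analysis of clinical outcomes, the exploratory comparison is to be made "using analysis of covariance or a suitable alternative", and "Ninety-five percent confidence intervals will be constructed for the between-group differences for each of the outcomes, adjusted for baseline".

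Under Sample size, "the sample size of 48 (with 24 participants in each arm) is considered to be sufficient to provide an estimate of variation in outcomes", and that estimate is meant for powering the definitive trial. Limitations and barriers repeats this purpose. No section mentions clustering by therapy group or therapist, an ICC or a design effect.

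**The concern.** Chilled participants in the same group share leaders, peers and sessions; ACTA participants do not. This is a partially nested design: one arm has a possible group-level variance component and the other has none from group delivery. Ordinary ANCOVA treats all 48 as independent. If outcomes within a therapy group are positively correlated, its standard error for the arm difference is too small.

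Two outputs are affected. The first is the exploratory intervals, which the protocol intends to compare with the literature. The second is what the study hands on. A definitive trial of the same two formats needs the outcome SD and also an allowance for grouping in one arm, and the protocol speaks only of the variation in outcomes.

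**Working it through.** **The plan's own figure.** The 48 (24 + 24) is set by precedent from earlier feasibility studies. No effect size, SD, ICC or power is stated, so there is no calculation to reproduce.

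**Inputs from the protocol article.** 24 per arm (Sample size); group size m = 4 to 6 (Chilled section), hence 24/6 = 4 to 24/4 = 6 groups; 95% confidence; baseline-adjusted ANCOVA (Analysis of clinical outcomes).

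**Assumed inputs.** ICC within therapy groups in the Chilled arm after baseline adjustment, ρ = 0.01 to 0.20; equal residual variance in both arms; no therapist clustering in ACTA. For the definitive-trial illustration only: d = 0.5, 80% power, two-sided 5%, equal allocation.

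**Formulas.**
- Design effect in the Chilled arm: DE = 1 + (m − 1)ρ.
- Correct SE / ANCOVA SE, equal arms: √((1 + DE)/2).
- Expected pooled variance / true variance: 1 − (m − 1)ρ/(2 × 23).
- Definitive trial, n per arm: (1 + DE) × ((1.960 + 0.842)/0.5)² = (1 + DE) × 31.4, rounded up. With DE = 1 this gives 63.

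Coverage was obtained by simulating ANCOVA with 24 per arm, 20,000 runs per setting. For m = 5 the groups were 5, 5, 5, 5 and 4.

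| m | ICC | DE | SE ratio | Coverage of nominal 95% CI | Pooled variance ratio | Definitive n per arm |
|---|---|---|---|---|---|---|
| 4 | 0.05 | 1.15 | 1.04 | 94.1% | 0.997 | 68 |
| 5 | 0.05 | 1.20 | 1.05 | 94.1% | 0.996 | 70 |
| 6 | 0.05 | 1.25 | 1.06 | 93.4% | 0.995 | 71 |
| 4 | 0.10 | 1.30 | 1.07 | 93.3% | 0.993 | 73 |
| 5 | 0.10 | 1.40 | 1.10 | 92.6% | 0.991 | 76 |
| 6 | 0.10 | 1.50 | 1.12 | 91.9% | 0.989 | 79 |
| 4 | 0.20 | 1.60 | 1.14 | 91.4% | 0.987 | 82 |
| 5 | 0.20 | 1.80 | 1.18 | 90.5% | 0.983 | 88 |
| 6 | 0.20 | 2.00 | 1.22 | 88.9% | 0.978 | 95 |

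At ICC 0.01 the SE ratio is 1.007 to 1.012. At ICC 0 simulated coverage is 95.0–95.3%, so the shortfalls come from the clustering.

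**Interval width.** The ANCOVA half-width is t(0.975, 45) × √(2/24) = 0.58 residual SD. It should be about 0.60–0.62 at ICC 0.05, 0.62–0.65 at 0.10 and 0.66–0.71 at 0.20, before any further widening for estimating a group variance from so few groups.

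**The SD handed on.** The lowest pooled variance ratio is 0.978, so the SD is at worst √0.978 = 0.989 of its true value. That alone moves the illustrative 63 per arm to 62 at most. The design effect moves it to 68–95.

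**Can this study estimate the ICC?** Hardly. With an observed ICC of 0.10, the exact F-based 95% interval runs from about −0.10 to 0.79 with four groups of six, and from about −0.17 to 0.67 with six groups of four.

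**The case against.** Four points count on the other side.

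- The wording allows an alternative to ANCOVA, and an analysis plan not shown here could add a group term. This stands: an independence analysis is the named default and is not fixed. But nothing in the article shows that the nesting was recognised, and a reader following the named model would ignore it.
- Under-coverage needs a positive ICC, which the documents do not give. This also stands, and the result is conditional. At 0.01 nothing of note happens, and at 0.05 coverage is still about 94%.
- The intervals decide nothing. Current trial, Sample size and Analysis of clinical outcomes all treat the between-arm comparison as exploratory, and none of the six Feasibility criteria uses a between-arm effect or its interval. This lowers the priority. It does not reach the second use, because supplying the variation for powering the definitive trial is a stated purpose of the sample.
- With four to six groups a random group variance is barely estimable, so a mixed model gains little. This stands for the ICC estimate. It argues for showing intervals over assumed ICCs, not for leaving clustering out.

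A reader might infer that the variance passed to the definitive trial is itself too small. The calculation does not support that: the marginal SD is essentially unbiased. Nor can one say that the definitive trial will be under-sized. The document contains no such calculation, and nothing in it rules out a design effect at that stage.

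**Conclusion.** The point holds in a limited form. The design is partially nested, the only model named ignores this, and clustering is not mentioned. For ICCs between 0.05 and 0.20 the correct standard error is 4–22% larger than the ANCOVA one, and coverage falls to between about 94% and 89%. The more useful loss is for planning. Without a group-arm design effect, an illustrative 63 per arm would stand where 68–71 (ICC 0.05) or 73–79 (ICC 0.10) are needed, an increase of about 8–13% or 16–25%.

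These sizes rest on the assumed ICCs, groups of four to six, 24 per arm, equal variances and, for the sample-size illustration, d = 0.5 and 80% power. Therapist clustering in ACTA is not covered, since the number of clinicians is unknown. Because the comparison is exploratory, this is a moderate-priority correction and does not threaten the feasibility conclusions.

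**What to change.** 1. Record therapy-group and clinician identifiers for every participant. They may be hard to reconstruct after delivery.
2. In Analysis of clinical outcomes, state that the between-arm intervals allow for therapy-group clustering in the Chilled arm. One option is a partially nested mixed model: baseline as covariate, random group effect in Chilled only, arm-specific residual variances, and Satterthwaite or Kenward-Roger degrees of freedom. Because four to six groups estimate the ICC poorly, the other option is to give the ANCOVA interval with its SE multiplied by √((1 + DE)/2) for assumed ICCs such as 0.05 and 0.10. If the arms end up unequal, use √((1/n_ACTA + DE/n_Chilled)/(1/n_ACTA + 1/n_Chilled)).
3. If an ICC is estimated, report it with its interval and do not use the point estimate alone.
4. In Sample size and Limitations and barriers, state that the definitive sample size will apply a group-arm design effect over a range of ICCs and will not rest on the SD alone.

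The cost is two identifiers and a few sentences. Recruitment, treatment and sample size do not change. The downside is slightly wider exploratory intervals and an imprecise ICC.

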### Analysis of economic outcomes

Suitability and acceptability of the economic measures will be assessed on the basis of both rates of responses at the end of the feasibility study and from young people’s and their parent/s/carer/s’ feedback. Proportions of responses to healthcare resource use and health outcome measure questions will be presented in separate tables for the ACTA and the Chilled Group arms. Missing data will be explored in order to establish whether this is due to lack of response to specific questions, to the measure altogether, or to loss of follow-up. Rates of this missing data will also be compared to that of clinical measures to assess patterns in the response of certain participants. For both quality of life measures (i.e. the EQ-5D-Y and the CHU-9D), utility scores and QALYs will be calculated and compared for both treatment groups to explore how sensitive each measure is to change over time. Adolescent self-report and parent/carer report on the young person will also be compared for the CHU-9D in order to assess any discrepancies in responses of the adolescents and their parent/s. Finally, variation in quality of life as derived from the EQ-5D-5 L will be reported and compared across both treatment groups.

